## 3. Methods and Design

### 3.1. Study Design

This is a multicenter, pragmatic clinical trial comparing real acupuncture intervention with no acupuncture to evaluate the treatment effects of acupuncture on the outpatient population of poststroke dysphagia. Owing to the characteristic of poststroke dysphagia patient and the nature of acupuncture, it is not feasible to implement the sham acupuncture in this study. The patients in acupuncture group and no-acupuncture control group will be in 1 : 1 allocation ratio. Subjects who are eligible in study and willing to accept acupuncture will be allocated to intervention group, while subjects eligible in study but refuse to have acupuncture treatment will be put on the no-acupuncture control arm. In the real acupuncture group, patients will receive acupuncture intervention in addition to conventional treatment. Real acupuncture group is defined as the group in the study that receives a series of sessions of acupuncture treatment which is being tested. The study will be conducted in several Chinese medicine clinics including The Pok Oi Hospital, The Chinese University of Hong Kong Clinical Center for Teaching and Research in Chinese Medicine (Shatin and Yuen Long), and The Yan Oi Tong, The Chinese University of Hong Kong Clinical Center for Teaching and Research in Chinese Medicine (Tuen Mun). Acupuncture treatment may also be conducted at the affiliated mobile clinics of these centers. This project is approved by both the Joint Chinese University of Hong Kong-New Territories East Cluster Clinical Research Ethics Committee (CRE-2012.236-T) and New Territories West Cluster Clinical Research Ethics Committee (NTWC/CREC/1281/14). Written informed consent is obtained from each participant. The study will be conducted according to ICH-GCP Guidelines. The study design is described in Figure 1.

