## 9. Secondary Outcomes

The secondary outcome measures include functional oral intake scale [21], swallow quality-of-life questionnaire in Chinese version [22], BMI [7], and adverse event report.

Functional oral intake scale, or known as swallow function scores, is a 7-point scale that describes the severity of swallowing dysfunction.

Swallow quality-of-life questionnaire in Chinese version consists of 12 items. The items covered all physical and psychosocial impact of the patients. Swallow quality-of-life questionnaire in Chinese version is chosen as secondary outcome because it is as sensitive, valid, and reliable as original version [22].

All adverse events as defined by the Ethics Committee will be fully recorded on the Adverse Event Page of the Case Report Form.

All functional oral intake scale, swallow quality-of-life questionnaire in Chinese version, and BMI will be assessed at baseline (before the intervention), the end of treatment (2 months after inclusion), and the end of follow-up period (2 months after treatment completion).

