## 11. Data Analysis

All analyses will be conducted according to the intention-to-treat principle. Descriptive statistics will be computed for each of the analyzed variables. For the primary outcome, chi square test will be used. All continuous variables such as swallowing time, swallow quality-of-life, and BMI will be analyzed using *t*-test where appropriate. Swallow function scores will be analyzed using Mann–Whitney *U* test. The possible relationship between some baseline data and main outcomes will be explored using multivariable analysis. All statistical tests will be two-sided, and *p* < 0.05 is considered statistically significant. The statistical software of SPSS (SPSS, SPSS Inc., Chicago, USA) version 20 will be used for the analysis.

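### The named tests for swallowing quality of life, BMI and oral intake use no baseline covariate, although the arms are self-selected and each outcome is measured at baseline

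*Protocol article*

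**What the plan says.** **Tests.** Section 11 (Data Analysis) states "All continuous variables such as swallowing time, swallow quality-of-life, and BMI will be analyzed using" a t-test, qualified as being used where suitable. It continues: "Swallow function scores will be analyzed using Mann–Whitney" U test. Section 9 (Secondary Outcomes) shows that these scores are the functional oral intake scale: "Functional oral intake scale, or known as swallow function scores, is a 7-point scale".

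**Baseline data.** Section 9 also states "All functional oral intake scale, swallow quality-of-life questionnaire in Chinese version, and BMI will be assessed at baseline (before the intervention"), with repeats at the end of treatment and at the end of follow-up.

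**Allocation.** Section 3.1 (Study Design) forms the arms by patient choice: those willing to have acupuncture receive it, and "subjects eligible in study but refuse to have acupuncture treatment will be put on the no-acupuncture control arm".

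**Adjustment.** Two places mention it. Section 11 says "The possible relationship between some baseline data and main outcomes will be explored using multivariable analysis". Section 12 (Discussion) names the absence of randomization as a main limitation. It gives gender, age, occupation, life style and time of stroke onset as examples of factors to be controlled, and promises to check comparability and adjust afterwards.

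**The concern.** In a randomized trial, leaving out the baseline value of an outcome costs precision but does not bias the comparison. Here patients who accept acupuncture may differ at entry from those who refuse it, in nutrition, swallowing severity or quality of life. A two-group test of follow-up values then carries part of any entry difference into the apparent treatment effect. The same tests also leave in the error term the between-patient variation that the baseline value could explain. The baseline values will already have been collected, so nothing is gained by leaving them out of the comparison.

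Section 11 also lists swallowing time among the variables to be analysed. It appears in neither section 8 (Primary Outcome) nor section 9.

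**Working it through.** The plan gives no effect size, SD or power for these outcomes, so there is no figure of its own to reproduce.

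**Inputs**
- n = 60 per arm analysed: section 10, where it is set for the primary outcome and then raised to 70 recruited per arm.
- Two-sided 5% level: section 11.
- Baseline–follow-up correlation ρ: not in the documents; assumed 0.3 to 0.9.
- Baseline difference between arms d, in SD units: not in the documents; assumed 0 to 0.5.
- No treatment effect, equal SDs, and arms that differ only in the measured baseline value.

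**Formulas (SD units)**
- Follow-up-only test: expected difference ρd; SE = √(2/n) = √(2/60) = 0.183.
- Change-score test: expected difference −(1−ρ)d; SE = √(2/n × 2(1−ρ)).
- Rejection rate = Φ(z − 1.96) + Φ(−z − 1.96), where z = |expected difference|/SE.

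Example, d = 0.3 and ρ = 0.7. Follow-up only: z = 0.21/0.183 = 1.15, rejection 21%. Change score: z = 0.09/0.141 = 0.64, rejection 10%.

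**Rejection rate with no treatment effect**

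| d (SD) | Test | ρ 0.3 | ρ 0.5 | ρ 0.7 | ρ 0.9 |
|---|---|---|---|---|---|
| 0 | either | 5% | 5% | 5% | 5% |
| 0.1 | follow-up | 5% | 6% | 7% | 8% |
| 0.1 | change | 6% | 6% | 6% | 5% |
| 0.3 | follow-up | 8% | 13% | 21% | 32% |
| 0.3 | change | 16% | 13% | 10% | 7% |
| 0.5 | follow-up | 13% | 28% | 48% | 69% |
| 0.5 | change | 37% | 28% | 19% | 9% |

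Change scores help when ρ is above 0.5, make no difference at 0.5, and do worse below it.

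**Simulation check.** This used 2,000 runs per setting, with ρ of 0.5, 0.7 and 0.9 and d of 0, 0.3 and 0.5. The t-test followed the table. The Mann–Whitney test was close to it (47% against 48% at ρ = 0.7, d = 0.5). ANCOVA rejected 4.5% to 5.7% of the time in all nine settings.

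**Precision.** ANCOVA multiplies the variance of the difference by about 1 − ρ², that is 0.91, 0.75, 0.51 and 0.19 at ρ = 0.3, 0.5, 0.7 and 0.9. The difference detectable with 80% power is (1.96 + 0.84) × 0.183 = 0.51 SD for the follow-up-only test. With ANCOVA it falls to 0.49, 0.44, 0.37 and 0.22 SD.

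**BMI illustration** (assumed SD 4 kg/m², ρ = 0.9). The SE is 4 × 0.183 = 0.730 follow-up only, 0.730 × √(1 − 0.81) = 0.318 with ANCOVA, and 0.730 × √0.2 = 0.327 for change scores.

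**The case against.** **The t-test may be on changes.** Section 11 does not say that follow-up values are compared. With three visits, a t-test on change from baseline is a natural reading, and it uses the baseline. In the BMI illustration it recovers nearly all the precision (0.327 against 0.318) and cuts the false-positive rate at 0.3 SD imbalance from 32% to 7%. This stands for a highly correlated outcome. It does not hold generally: at 0.5 SD imbalance change scores still reject 28% of the time at ρ = 0.5 and 19% at ρ = 0.7. Nothing in the documents supports a high correlation for quality of life or oral intake, in patients recruited up to 12 months after stroke. The silence on what is tested is itself part of the problem.

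**Adjustment is planned.** The authors admit the limitation and promise adjustment, and a condensed article may leave covariates to an analysis plan that is not shown. A missing covariate list would therefore be no finding. But the article does name the tests for these outcomes, and the named tests do not fit the design it describes. The multivariable analysis is exploratory and tied to the main outcomes. The Discussion names no model and no outcome, and its example factors do not include baseline BMI, quality of life or oral intake. Read together, section 11 specifies unadjusted tests and section 12 promises adjustment.

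**A stronger reading.** A reader might infer that these tests would mostly re-detect differences present at entry. The documents do not support that, since they give neither a correlation nor an imbalance. In the table a follow-up-only test rejects more than half the time only at ρ = 0.9 with d = 0.5. At 0.1 SD imbalance it stays at 5–8%.

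**Conclusion.** The point holds as one of exposure and lost efficiency, not of demonstrated bias. In self-selected arms, the tests named for quality of life, BMI and oral intake take no baseline covariate, and the adjustment language elsewhere does not fill the gap for these outcomes. If follow-up values are tested and there is no effect, the false-positive rate runs from 5% with balanced arms to 69% in the most adverse assumed case.

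The near-5% rate for ANCOVA rests on arms that differ only in the measured baseline value. If untreated arms would instead keep their entry gap d, ANCOVA would leave a difference of (1−ρ)d, while a follow-up-only test would carry all of d. Baseline adjustment is thus an improvement, not a substitute for randomization.

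Only secondary outcomes are affected, so the change should be made but is not critical. The swallowing-time mismatch is a separate inconsistency and adds nothing to the argument on bias.

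**What to change.** - For quality of life and BMI, make the treatment comparison an ANCOVA: follow-up value regressed on arm and the outcome's own baseline value.
- For the functional oral intake scale, use an ordinal regression on arm and its baseline value.
- In each model, include a set of prognostic factors fixed before the data are examined, drawn from those the Discussion already lists (for example age, gender and time since stroke onset). This set has to be stated in its own right: the primary test is a chi-square, so there is no primary model to borrow covariates from.
- State that these models do not remove confounding by unmeasured factors.
- Reconcile section 11 with section 12, so that the adjusted analysis is either the stated comparison or clearly secondary to it.
- Reconcile swallowing time in section 11 with the outcome lists in sections 8 and 9: define it as an outcome or remove it.

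The cost is wording. The baseline values are already scheduled for collection, and no extra patients or visits are needed.

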## 12. Discussion

This pilot study is designed to evaluate the effectiveness and the safety of acupuncture for poststroke dysphagia. As the purpose of our pilot study is to assess the effectiveness and safety of acupuncture in managing poststroke dysphagia within the healthcare setting in Hong Kong, the pragmatic design is deemed appropriate. A routine supportive and rehabilitative treatment group without acupuncture is designed as a control group instead of sham acupuncture, as it is unrealistic to ask the stroke patients to receive sham acupuncture.

Due to the safety consideration and feasibility, RBHOMS is to be selected as the primary outcome. RBHOMS is widely used as bedside assessment in dysphagia patient. It is a noninvasive investigation, and the time required to perform this test is about 10 minutes. As it will not bring too much burden to the patients, it is anticipated that the compliance of patients in the control arm would be high.

The functional oral intake scale, coupled with swallow quality-of-life questionnaire in Chinese version, BMI, and adverse events report are to be used as secondary outcome. The functional oral intake scale is an ordinary rate scale to assess the swallowing function of a patient. It is an auxiliary instrument to assess swallowing function of the patients. Previous study [20] illustrated that swallow quality-of-life questionnaire in Chinese version is a valid, effective, and sensitive tool to assess the physical and psychosocial impact in dysphagia patient of Chinese population.

The strength of our pilot study design is the pragmatic approach. This study mimics the real-world clinical situation based on Hong Kong healthcare setting. Standard acupuncture treatment protocol is obtained by the consensus of our acupuncture expert panel. Although, in real-world setting, most acupuncturists will individualize their acupuncture points selection and manipulation based on TCM theory. However, considering the consistency and replicability of the trial, a standardize acupuncture treatment protocol is chosen. Even that standardized regular acupuncture points are adopted, all enrolled participants will be classified into two subtype syndromes according to diagnosis criteria and different additional acupuncture points will be punctured individually.

Blinding is a crucial measure to assure the quality of the trial. All outcome assessor and statistician will be kept blind throughout the whole process. We will minimize the interaction between the patients and outcome assessors. Neither the RBHOMS assessor nor the staff who administer the questionnaire knows the group allocation of the participants.

One main limitation of this study is lack of randomization. Randomization is a key procedure to minimize the selection bias and ensure the comparability of all parameters between the intervention group and control group. However, concerning the timeframe and budget of our pilot study, nonrandomization approach will be utilized. To reduce the selection bias of our study, subjects will be recruited from different sources, including hospitals, speech therapy outpatient clinics, and Chinese medicine clinics. Moreover, all the prognostic factors and baseline characteristics of participants such as gender, age, occupation, life style, and onset time of stroke will be controlled in both acupuncture group and nonacupuncture control group. All data will be collected to examine the baseline comparability and explore the possible sources of dissimilarity and make proper statistical adjustment later.

As for all clinical trials, subject recruitment is one of the most critical factors for the trial's successful implementation. In our study, various venues and approaches will be utilized to augment the subject recruitment process. Free Chinese medicine consultation will be provided to control arm participants as an incentive. In addition, we will also hold promotional talks in the Chinese medicine clinics to facilitate the recruitment process. Moreover, we may also place advertisements on local newspapers and contact the stroke patients association to boost subject recruitment if recruitments from hospitals and Chinese medicine clinics turn out to be undesirable.

Nonetheless, most of potential subjects of this study are stroke sufferers. They always have other complications, such as immobility. In order to reduce the dropout rate and to enhance the compliance of patients, some treatment sessions may be conducted at affiliated mobile clinics.

This pilot study is the first large scale, multicenter controlled trial focusing on the acupuncture for poststroke dysphagia, which is one of the common complications of stroke patient. Although there is some limitation of the study, the findings of this project are able to provide an early evidence for the effectiveness of acupuncture treatment in enhancing swallowing function and life quality of poststroke dysphagia patients.

## Figures and Tables

**Figure 1 fig1:**
[figure not shown]
Study flow chart.

**Table 1 tab1:** Locations, indications, and manipulations of the acupoints selected for the project.

Points	Location	Indications	Manipulation
GB20 (Feng Chi)	In the depression between m. sternocleidomastoideus and m. trapezius, level with Fengfu (DU 16) point (on the Du meridian, 1 cun above the posterior hairline). [If the hairline is not easily determined, the level of bilateral earlobe tip connection will be used.]	Headache, stiff neck, red and painful eyes, nose bleeding, tinnitus, stroke, swallowing difficulty, deviated mouth, and eyes.	Puncture at a depth of 0.8–1.2 cun with the needle tip pointing towards the throat. After obtaining needling sensation, rotate the needles with reinforcing techniques (rotating 180°–270° at 30 times/min for 30 seconds) till the needling sensation radiating to the whole tongue and throat.

GB12 (Wangu)	On the head, in the depression posterior-inferior to mastoid process.	Headache, neck stiffness, toothache, facial palsy.	Similar to GB20

CV23 (LianQuan)	With the patient's head slightly tilting backward, the point is directly above the Adam's apple and at the midpoint of the upper border of the hyoid bone.	Swelling and pain in the tongue, excessive salivation, stroke with stiffness of the tongue, sudden loss of voice, difficulty in swallowing.	Insert obliquely for about 1.0 cun towards the root of the tongue, followed by applying mild lifting and thrusting technique for about 1 min till soreness and distending sensation (de qi) is felt in the tongue and throat.

Shanglianquan	1 cun above CV23 (with the patient in a sitting position and the patient's head slightly tilting backward, the point is directly above the Adam's apple, and on the midpoint of the upper border of the hyoid bone).	Alalia, sore throat, difficulty in swallowing, difficulty in speech	Insert the needle obliquely to a depth of 1.0–1.5 cun towards the root of the tongue. Then followed by mild lifting and thrusting the needle for around 30 seconds until soreness and distending sensation is felt in the tongue and throat.

Hangsang	On the posterior wall of the throat.	Sore throat, difficulty in speech.	Patient is asked to open the mouth, with the tongue pressed by a tongue depressor to expose the posterior wall of the throat clearly. Then a needle of 75 mm in length will be applied to prick the posterior wall of the throat at the depth of about 0.15 cunfor 4 times. After the needle is withdrawn, the patient is asked to move the tongue in and out for 10 times.

Lower 2/5 of the motor zone of the scalp	The motor zone is a line connecting the following two points: the first is 0.5 cm posterior to the midpoint of the anteroposterior midline over the vertex; the second is the intersection of the lateral eyebrow-occiput line with the anterior border of the hairline at the temple. The motor zone can be divided into 5 portions.	Facial paralysis, swallowing difficulty.	Insert the needle transversely at 15° angle to the skin surface and push the needle to about 1.0 cun in depth, then use twirling method (rotating 180°–270° about 200 times/min) to manipulate the needle for about 30 seconds.

DU20 (Bai Hui)	7 cun above the midpoint of the posterior hairline, or at the junction of the midline at the vertex with the line joining the two ear apexes.	Headache, tinnitus, vertigo, stroke with difficulty to speak.	Puncture obliquely at an angle of 30 degrees to a depth of 0.5 to 0.8 cun, then use rotating motion (rotating 180°–270° at about 200 times/min) to manipulate the needle for about 30 seconds before withdrawing the needle.

LI4 (HeGu)	On the dorsum of the hand, between the first and second metacarpal bones, approximately in the middle of the second metacarpal bone on the radial side.	Swollen and sore throat, headache, toothache, deviated mouth and eye, fever, delayed labour.	Puncture perpendicularly for 0.5 to 1.0 cun, then apply for 30 seconds reinforcing technique with the lifting and thrusting movement (strong thrusting and gentle lifting for short duration with small amplitude and low frequency).

HT5 (Tongli)	1 cun above the shenmen point, which is at the medial end of the transverse crease of the wrist, in the depression on the radial side of the tendon of the flexor carpi ulnaris.	Painful and swollen throat, sudden loss of voice, stiff tongue with difficulty in speech.	Puncture perpendicularly to a depth of 0.5cun, then apply reinforcing technique with the lifting and thrusting movement for 30 seconds.

ST40 (Fenglong)	8 cun above the external malleolus, 2 cun lateral to the anterior crest of the tibia.	Headache, cough and stroke with phlegm as the pathogenic cause.	Puncture perpendicularly for 1.5 cun, then apply reducing technique by lifting and thrusting the needle (gentle thrusting and strong lifting with large amplitude and high frequency) 30 seconds.

LR3 (Taichong)	On the dorsum of the foot, in the depression distal to the junction of the 1st and 2nd metatarsal bones.	Headache, dizziness, blurred vision, deviated mouth, stroke.	Puncture perpendicularly for 0.5–1.0 cun, then apply reducing techniques by lifting and thrusting the needle for 30 seconds.

KI3 (Taixi)	At the depression between the medial malleolus and the tendon calcaneus.	Sore throat, deafness, coughing blood, impotence, frequent urination and lumbar pain.	Insertion perpendicularly for 0.5–1.0 cun, then apply for 30 seconds reinforcing technique with the lifting and thrusting movement.

UB23 (Shen Shu)	Level with the lower border of the spinous process of the 2nd lumbar vertebra, 1.5 cunlateral to the posterior midline.	Blurred vision, deafness, tinnitus, edema and lower back pain.	Straight insertion for 0.5–1.0 cun, then apply for 1 min reinforcing technique with the lifting and thrusting movement.

## Abbreviations

BMI: Body mass index
RBHOMS: Royal Brisbane Hospital Outcome Measure for Swallowing
TCM: Traditional Chinese medicine.
